##### SSUAD controls inclusion criteria

Controls had to meet the following inclusion criteria to be eligible for study enrolment:
Able to provide written informed consent and understand all relevant study components.Aged 18 years or older.Willing and able to provide a urine sample.

##### SSUAD controls exclusion criteria

Controls presenting with any of the following criteria were not included in the study:
Possible pneumonia or another respiratory infectious disease or signs of pneumococcal disease, with evidence of active infection.Residing in a long-term care facility.Known bronchial obstruction or a history of post-obstructive pneumonia. Chronic obstructive pulmonary disease was allowed, provided there had not been an exacerbation within the 3 months prior to enrolment.Primary lung cancer or another malignancy metastatic to the lungs.Fever (temperature of ≥38.0 °C measured by a healthcare provider).Significant immunosuppressive disease such as AIDS, leukaemia, etc.Received PCV and/or pneumococcal polysaccharide vaccine (PPSV) within the past 30 days.

#### Clinical and laboratory methodology for prospective study

##### Nasopharyngeal swab collection and testing

Nasopharyngeal swabs are collected and stored according to WHO guidelines [41]. Swabs are collected by designated trained nurses at each hospital and placed into a vial containing STGG medium and stored in a refrigerator in the specimen collection area at each hospital. Utilising the same transport and processing procedures as the paediatric surveillance project [27] swabs are transported to the National Center for Communicable Diseases (NCCD) microbiology laboratory, where they are vortexed and aliquoted. Samples shipped to the Murdoch Children’s Research Institute (MCRI) are screened for pneumococci using qPCR [37]. Samples that contain pneumococci undergo molecular serotyping by microarray following culture-amplification [42]. Testing for RSV and influenza will be conducted at the NCCD Virology laboratory or MCRI, using a validated multiplex real-time RT-PCR which has been validated in other studies in Vietnam [43] and in the paediatric surveillance project in Mongolia [27].

##### Urine processing

Urine samples from adult cases enrolled prospectively in the adult surveillance programme, will be tested at the NCCD bacteriology laboratory in Mongolia using a rapid pneumococcal urinary antigen test (BinaxNOW®, Alere North America, Orlando, Florida). The BinaxNOW® *Streptococcus pneumoniae* test is an immunochromatographic membrane assay test used to detect pneumococcal soluble antigen in human urine. It detects the pneumococcal C-polysaccharide which is found in the cell wall and is common to all serotypes. BinaxNOW® urine testing conducted at the NCCD bacteriology laboratory will be conducted by two designated trained laboratory technicians according to study standard operating procedures to ensure consistency of results.

Additional urine will be frozen in ultra-low temperature (− 70 °C) freezers before being shipped to the Pfizer Laboratories, Pearl River, USA for pneumococcal testing using multiplex SSUAD assays that assesses the 13 serotypes in PCV13 (UAD1) [4] and the additional 11 serotypes in 23-valent pneumococcal polysaccharide vaccine (PPSV23) (UAD2) [3]. Positivity cut-off limits for the SSUAD assay will be established based on antigen concentrations read off a standard curve for each serotype using the 400 urine specimens collected from control subjects as described above. While UAD cut-points have only rarely been reset based on evaluation of local healthy control subjects, this step ensures test validity and high specificity.

##### Processing of other samples and CXRs

Any pleural fluid collected will be cultured and blood cultures will be taken according to standard clinical practice. Blood culturing practices may differ between the four hospitals and will not be done for all adult pneumonia cases. Pleural fluid will be tested by *lytA* qPCR in Mongolia if possible, otherwise shipped and tested at MCRI.

CXRs will be performed and archived for all pneumonia cases. CXRs will be digitalised and uploaded in an electronic database for re-reading according to adapted standardised WHO criteria. CXRs will be reread by two independent radiologists who are trained in WHO methodology, and results will be entered into the electronic database. Any disagreement in results between the two readers will be resolved by a third radiologist.

#### Statistical methods

##### Sample size estimation

Power calculations were based on a generalised linear mixed model to account for the staggered vaccine introduction and clustering within the four study districts [44]. Calculations assumed that for clinical pneumonia the data from 2015 to 2022 would be included. Calculations assumed an average of 13,271 person-years in each district per monthly interval and an intra-cluster (i.e. intra-district) correlation of 0.2. Considering the timing of vaccine introduction and a significance level of 0.05, the study has 92% power to detect a 20% decrease in severe pneumonia incidence rate from 9.8 to 7.8 per 10,000 person-years. Calculations were performed in Stata version 15 using the “stepped wedge” command [45].

##### Statistical analysis plan

The primary analysis endpoint will be the change in severe clinical pneumonia incidence rate ratios (IRR) comparing the pre- and post-vaccine periods over 87 months in all four districts (Songinokhairkhan and Sükhbaatar with 17 months pre-PCV and 70 months post-PCV; Bayanzürkh with 30 months pre-PCV and 57 months post-PCV; and Chingeltei with 38 months pre-PCV and 49 months post-PCV). Retrospective data from 2015 will be used to contribute to pre-vaccine case numbers for the primary outcome. See Fig. 1 showing the schematic study timelines.

**Fig. 1 Fig1:**
[figure not shown]
Schematic diagram of study design and timelines

The outcome variable for this analysis will be monthly district-level counts of severe clinical pneumonia. The IRR will be estimated using a mixed effects Poisson loglinear regression model (or a negative binomial model if there is over-dispersion) fitted to monthly counts, with log-transformed population denominators included as an offset. The model will include a fixed effect for PCV13 (indicator variable for PCV13 introduction which will depend on the district as PCV13 introduction was staggered), a fixed effect for time (time since study commencement in months) to account for temporal trends, and a random effect for district. The PCV13 term will be exponentiated to obtain the incidence rate ratio for the vaccine effect. This model assumes that there is uniform vaccine impact across the districts. Sensitivity analyses will explore whether the vaccine impact differs across districts and will include seasonality and employ changes in vaccine coverage as opposed to fixed PCV13 effects. A subgroup analysis will explore rate changes in different age groups (18–25, 26–45, 46–65 and > 65 years). We will also do a sensitivity analysis with a 1 year “lag period” for indirect PCV effect (as we don’t expect the indirect effect to be instantaneous).

For the secondary pneumonia endpoints, no pre-PCV13 radiological and urine data are available. Consequently, we will explore trends over time in the post-PCV13 introduction period, incorporating district and time since PCV13 introduction.

We will conduct a nested case-control analysis (“test-negative design” [46]) to measure the indirect PCV13 vaccine effectiveness among adults living with children eligible to be vaccinated with PCV13. The model will account for district and time since vaccine introduction. We will compare the odds of receiving PCV13 among household children between cases and controls, defined as: 1) adults with vaccine type (cases) versus non-vaccine type pneumonia (controls), 2) among adults who had a CXR, WHO defined radiological confirmed pneumonia (cases) versus no radiological pneumonia (controls) and 3) among adults who had pulse oximetry, hypoxic (cases) versus non-hypoxic (controls) pneumonia.

Numbers of cases hospitalised with cardiovascular or renal disease in the four district hospitals will be collected from 2015 to 2022 as two separate “control” conditions to help determine whether changes over time are related to secular trends or vaccine effects. We will include the control condition in the model for severe clinical and clinical pneumonia as a covariate. We will have an “uncontrolled” model as the main analysis, and a “controlled” model as a sensitivity analysis.

Chi-square tests will be used to evaluate changes in PCV13 and non-PCV13 serotypes over time, comparing the proportions of both identified in year one to year three, for each age group.

An interim analysis will be conducted for the primary clinical outcome in December 2020 and will be conducted in the same way as the final analysis except for a shorter follow-up time (71 months). The final analysis, which will include all primary and secondary objectives as well as laboratory data (nasopharyngeal swabs and urine), will be conducted once data collection, data cleaning and laboratory analysis has been completed - planned end of 2022.

A separate detailed statistical analysis plan including details related to the secondary analyses, nested case-control study and changes to model assumptions considered for sensitivity analyses has been approved by the study statisticians.

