Viruses and pneumococci in the upper airway may interact to lead to a viral, pneumococcal or combined lower respiratory infection [16]. For example, many deaths during the 1918 influenza pandemic were attributed to secondary pneumococcal pneumonias [17]. In children, studies corroborate an association between respiratory syncytial virus (RSV) and pneumococcus [18] with declines reported in RSV- and influenza-associated pneumonia hospitalisation rates following PCV introduction [19]. Viral and viral-bacterial co-infections are not uncommon in adults with pneumonia [20, 21]. In adults with pneumonia who tested RSV-positive, those who had a bacterial coinfection, were more likely to have a more severe outcome (longer length of hospitalisation and more frequent ICU admission) than those who had no coinfection [22].

In Mongolia in 2015, respiratory disease was amongst the five leading causes of hospitalisations in all age groups (345.6 per 10,000 population per year), with 44% of these admissions due to pneumonia. Respiratory disease was also amongst the top five causes of mortality (2.0 per 10,000 population) in the same year [23]. There is strong seasonal variation in pneumonia incidence [24], with the peak season occurring during the winter months (approximately October until April), exacerbated by extreme winter temperatures with high domestic coal use and resultant air pollution [25]. Published data from Mongolia document influenza burden [24] but data on the burden and severity of RSV in adults is more limited in the region [26].

The Mongolian Government introduced 13-valent PCV (PCV13) using a 2 + 1 infant schedule (age 2, 4 and 9 months) in a phased approach over 3 years from June 2016 starting with the capital city of Ulaanbaatar and ending with introduction into the provinces from April 2019. Enhanced hospital surveillance for paediatric pneumonia was initiated in four district hospitals and one tertiary hospital from April 2015 to monitor the direct impact of PCV13 introduction [27, 28]. Community carriage surveys in infants and toddlers showed a reduction in PCV13 serotypes 1 year post-introduction [29]. There are currently no data on the prevalent pneumococcal serotypes in adults in Mongolia.

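### The primary model omits seasonality despite unequal winter exposure before and after introduction, so with its linear trend it yields a spurious vaccine benefit of about 5 to 12%

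*Protocol article*

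**What the plan says.** The Statistical analysis plan subsection of the article (text under Fig. 1) specifies a "mixed effects Poisson loglinear regression model (or a negative binomial model if there is over-dispersion) fitted to monthly counts". Besides the PCV13 indicator it has "a fixed effect for time (time since study commencement in months) to account for temporal trends, and a random effect for district". No seasonal term is listed. Season appears afterwards: "Sensitivity analyses will explore whether the vaccine impact differs across districts and will include seasonality".

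The Background states "There is strong seasonal variation in pneumonia incidence", "with the peak season occurring during the winter months (approximately October until April".

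The analysis runs from January 2015 to March 2022, 87 months. The two first districts are analysed "with 17 months pre-PCV and 70 months post-PCV", the third "with 30 months pre-PCV and 57 months post-PCV", and the fourth with 38 and 49 months. The December 2020 interim uses the same model on 71 months.

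Under Sample size estimation, "Power calculations were based on a generalised linear mixed model to account for the staggered vaccine introduction and clustering", and the stated power is 92% for a fall from 9.8 to 7.8 per 10,000 person-years.

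**The concern.** A monthly series with a strong winter peak is compared across windows of 17, 30 and 38 months before introduction, none a multiple of 12. If winter months are over-represented before introduction, and the only time term is a straight line, part of the seasonal cycle can be credited to the vaccine. The headline IRR would then favour PCV13 with no effect present, at the interim as well as at the final analysis. A season-adjusted sensitivity analysis would show the discrepancy but would leave the biased figure as the primary result.

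A related question is precision. The article names influences that can move all four districts in the same month: the 2015/16 measles outbreak, COVID-19 restrictions, and yearly influenza and RSV variation. The stated model has no term for a deviation shared across districts.

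**Working it through.** **Inputs.** From the article: 87 months from January 2015; introduction after months 17, 17, 30 and 38; winter taken as October to April; 13,271 person-years per district-month; 9.8 per 10,000; intra-district correlation 0.2; significance level 0.05 (taken as two-sided). Assumed, because the article gives no figure: winter:summer rate ratio 1.5 to 3; shared monthly shocks with log-SD 0.1 to 0.2 and lag-one autocorrelation 0 or 0.5.

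**Stated power.** Stepped-wedge variance (Hussey-Hughes) with 4 districts, 87 periods, total variance p(1−p) averaged over the two rates, and 0.2 of it between districts:
- a separate fixed effect for every month: 92.5% (91.4% if 7.84 replaces 7.8);
- a linear time term only: 99.6%.

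The stated 92% is therefore reproduced with study-month effects and not with the linear term of the primary model.

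**Winter months before and after introduction.**

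| District(s) | Before | After |
|---|---|---|
| Songinokhairkhan, Sükhbaatar | 11/17 = 64.7% | 41/70 = 58.6% |
| Bayanzürkh | 18/30 = 60.0% | 34/57 = 59.6% |
| Chingeltei | 23/38 = 60.5% | 29/49 = 59.2% |

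**Bias.** The fitted model is log E(count) = district + β·PCV13 + γ·time, with districts entered as fixed effects. It was fitted to expected counts with a two-level season and no vaccine effect. The table shows exp(β), which should be 1.

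| Winter:summer ratio | Stated model | Without the linear term | With month-of-year terms |
|---|---|---|---|
| 1.5 | 0.947 | 0.989 | 1.00 |
| 2 | 0.916 | 0.982 | 1.00 |
| 3 | 0.879 | 0.973 | 1.00 |

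The imbalance alone gives only 1 to 3%. The rest arises with the linear trend. The series starts and ends in winter, so the fit uses a rising trend (factors of 1.09, 1.15 and 1.22 over the 87 months) and a compensating downward step at introduction. A true IRR of 0.80 would be estimated as 0.80 × 0.916 = 0.73 at ratio 2 and 0.80 × 0.879 = 0.70 at ratio 3. At the 71-month interim the null IRR is 0.946 and 0.921 at those ratios.

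**Standard error of the stated model.** Simulation with about 13 cases per district-month (13,271 × 9.8/10,000 = 13.0), a 2:1 season, autocorrelation 0.5 and overdispersion-scaled standard errors for log IRR:

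| Shared shock log-SD | True SD | Model SE |
|---|---|---|
| none | 0.053 | 0.079 |
| 0.1 | 0.071 | 0.081 |
| 0.2 | 0.109 | 0.088 |

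Repeat runs gave true SDs of 0.066 at log-SD 0.1 and 0.099 to 0.104 at log-SD 0.2. Unmodelled season inflates the estimated dispersion, so the SE is too wide until the shocks are large.

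**Standard error once season is modelled.** At log-SD 0.2 and autocorrelation 0.5 the true SD is about 0.10 against a model SE of 0.064. Across log-SD 0.1 to 0.2 with autocorrelation 0.5, type I error is about 9 to 27%. Without autocorrelation it is 4.8% at log-SD 0.1 and 11.5% at 0.2.

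**Fixed study-month effects.** Null IRR about 1.00, true SD 0.07 to 0.075, model SE about 0.07, type I error about 4 to 7% (100 to 200 runs per setting).

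**The case against.** The strongest reply is that season has not been forgotten. A season-adjusted sensitivity analysis is planned, as is a model adjusted for control conditions; COVID-19 data are being collected, and a separate analysis plan exists. That plan is described as covering secondary analyses, the case-control study and changed assumptions for sensitivity analyses. The article itself fixes the primary model and places season outside it, so the bias point stands as a stated choice.

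A reader might infer more: that the primary model's intervals are already too narrow and its type I error about 10 to 24% through shared shocks. The article does not support that. Such rates belong to models with season terms. In the season-free model, with the negative binomial or scaled variance that a 2:1 season would almost certainly trigger, the SE is too wide with no shocks or log-SD 0.1. It becomes too narrow only at about log-SD 0.2. Over-rejection there (8 to 13% at log-SD 0 to 0.1) comes mainly from the bias.

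The shock size and autocorrelation are assumptions too, and so is the event count. About 13 cases per district-month means 13 × 4 × 12 = 624 severe cases a year, which is 51 to 73% of the 850 to 1,220 eligible pneumonia cases a year in the chart review. At an assumed 5 per district-month, type I error with season terms is about 6 to 9% at log-SD 0.1 and 15% at 0.2: smaller, but not gone. The expected-count bias does not depend on the event count.

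**Conclusion.** The bias point holds. At every seasonal ratio tried, the stated primary model leans towards a vaccine benefit: about 5, 8 and 12% at ratios of 1.5, 2 and 3, against a 20% target. Direction and mechanism follow from the article's own calendar and model; the size rests on an assumed ratio and a two-level season. Winter imbalance alone does not explain it, since two districts are nearly balanced and the linear trend contributes most of the effect.

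The precision point is conditional. It applies once season is in the model, and depends on shared shocks whose size and persistence the article does not give. It is no ground for saying that the intervals as planned are too narrow in general.

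**What to change.** 1. Put month-of-year terms (11 indicators, or harmonics) in the primary model for both the interim and the final analysis, and keep the season-free model as a sensitivity analysis. This removes the bias and needs no new data.
2. Fit fixed study-month effects, replacing the linear and month-of-year terms, either as the primary model or as a prespecified key analysis. This removes the bias, absorbs shocks common to the four districts, and aligns the analysis with the structure that reproduces the 92%.
3. If a random study-month effect with serial correlation is preferred, check its type I error by simulation first; it was not tested here.

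The cost is analysis-plan wording and, for item 2, a wider interval: SE about 0.07 against 0.053 with month-of-year terms and no shocks. On the Poisson log scale at the planned rates, the SE with study-month effects is 0.075, so power for an IRR of 0.80 is Φ(0.223/0.075 − 1.96), about 85%. With linear time only, the SE of 0.056 gives about 98%, but that precision belongs to a biased estimate.

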To evaluate the association between childhood PCV13 introduction and the trends in incidence of (a) clinical pneumonia or (b) hypoxic pneumonia only (see case definition) in adults 18 years and older in four districts of Ulaanbaatar over a 7 year period (Jan 2015 – Mar 2022).To evaluate the association between childhood PCV13 vaccination (during the early [2019–2020] and late [2021–2022] PCV13 introduction period) and the trends in adult pneumonia (see case definition) in four districts of Ulaanbaatar using the following endpoints: (a) all radiologically confirmed pneumonia, (b) definite pneumococcal pneumonia and (c) VT-pneumonia with a chest radiograph (CXR) consistent with CAP based on clinical assessment at time of hospitalisation.To evaluate the association between childhood PCV13 introduction (during the early and late PCV13 introduction period) and the trends in the detection and density of pneumococci in the nasopharynx of adults admitted with pneumonia.To assess changes in the detection of pneumococcal serotypes (VT and non-vaccine type [NVT]) associated with adult pneumonia in an era of ongoing childhood PCV vaccination.Among adults hospitalised for pneumonia, who have children of vaccine eligible age living in the household, to compare adult cases and controls with respect to having a child in the house who received one or more doses of PCV13 compared with households having all PCV13-unvaccinated children. The case-control comparison will be done for three subgroups: VT (case) compared with NVT pneumococcal pneumonia (control); end-point radiologically-confirmed pneumonia (case) compared with other radiologic findings (control); hypoxic (case) compared with non-hypoxic (control) pneumonia.To evaluate the association between PCV13 introduction in children on the trends in incidence and severity of adult pneumonia associated with viral pathogens (RSV or influenza) in four districts of Ulaanbaatar, during the early and late PCV13 introduction period, for the following endpoints: incidence of severe clinical pneumonia, clinical pneumonia, and radiologically confirmed pneumonia associated with RSV or influenza.

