### Study setting

Mongolia has a well-structured health system with a clear referral pathway from primary family healthcare centres to secondary district hospitals, and finally tertiary hospitals for severe or complicated cases [30]. Most adults access public health care and most pneumonia cases are captured by the public health services in district and tertiary care facilities [23, 30, 31]. Hospital care is accessible with primary and secondary facilities in each district and payment is based on income. Private care and self-referral incur significant cost for individual patients.

Active hospital-based surveillance for adult pneumonia was established in 2019 in four district hospitals in four districts of Ulaanbaatar (Songinokhairkhan, Sükhbaatar, Bayanzürkh and Chingeltei). These are the same four districts with ongoing enhanced paediatric pneumonia surveillance. These four districts are the largest districts of Ulaanbaatar containing 70% of the population of Ulaanbaatar with a mixture of areas with formal and traditional informal (ger) housing. The vast majority of adult pneumonia cases in the four districts under study are expected to be captured by the surveillance programme [23, 30, 31]. Annual district-specific denominator data are available from the Mongolian National Statistics Office, allowing us to calculate incidence rates for our four study districts.

As part of the routine childhood immunisation schedule, two study districts had PCV13 introduced in June 2016 (Songinokhairkhan, Sükhbaatar), one district in July 2017 (Bayanzürkh) and the fourth district in March 2018 (Chingeltei). Catch-up campaigns, for children 12–23 months, with two PCV doses were instituted in 2016 and 2017, but not in 2018 [27]. There is currently no licensure or recommendations for adult pneumococcal vaccination in Mongolia, and the pneumococcal polysaccharide vaccine is not available in-country.

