### Study design

The surveillance programme includes both retrospective (Jan 2015 - Feb 2019) and prospective (March 2019–March 2022) data collection. The study has a number of different components, including prospective pneumonia hospital-based surveillance with a nested case-control study, retrospective pneumonia chart review, data collection regarding other clinically relevant interventions and trends in cardiovascular and renal disease admissions as “control” conditions, and enrolment of controls without evidence of respiratory disease for validation of the urine antigen test [4].

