#### Retrospective pneumonia chart review

##### Chart review procedures

To provide additional baseline data on adult pneumonia admissions in the four districts, including inter-district variability in the incidence of clinical pneumonia prior to PCV13 introduction, we undertook a retrospective chart review of all adult pneumonia admissions to the adult hospitals in these districts from January 2015 to the start of prospective adult hospital-based surveillance in March 2019. Data extraction was undertaken by trained staff and included clinical data, demographic data, district and subdistrict (khoro) of residence, age, date of birth, length of hospital stay, outcome and severity markers. No urine, nasopharyngeal swabs or digital CXRs were available for this period.

Staff reviewed admission registers for potential pneumonia admissions and then reviewed the relevant medical records to confirm whether patients met predefined pneumonia case definitions. Overall respiratory admission numbers and pneumonia admission numbers were also collected. To ensure that no cases were missed during the retrospective review period, staff retrieved all medical records for review where any respiratory system disease diagnosis was recorded in the admission log records to confirm whether the patient had pneumonia which met the study case definition or not. In addition, all intensive care unit (ICU) admissions and deaths were reviewed to ensure that severe disease cases were not missed. The medical records were analysed for the same severity markers as those recorded prospectively. The definition of severe clinical pneumonia remained standard across the pre- and post-PCV period.

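### For endpoints with prospective data only, the trend in time since PCV13 introduction is in effect a calendar trend and cannot be read as an association with PCV13

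*Protocol article*

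**What the plan says.** The Study objectives frame the radiological, definite pneumococcal and vaccine-type (VT) endpoints this way: "To evaluate the association between childhood PCV13 vaccination" and trends in adult pneumonia, with 2019–2020 as the early period and 2021–2022 as the late one. The carriage and RSV/influenza objectives are also worded as associations with PCV13 introduction.

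The Statistical analysis plan section gives the limitation, "For the secondary pneumonia endpoints, no pre-PCV13 radiological and urine data are available", and then the analysis: "Consequently, we will explore trends over time in the post-PCV13 introduction period, incorporating district and time since PCV13 introduction". Chart review procedures says of January 2015 to the start of prospective surveillance: "No urine, nasopharyngeal swabs or digital CXRs were available for this period". Study design gives the window for the remaining data: "prospective (March 2019–March 2022) data collection". Study setting dates the introductions to June 2016 (two districts), July 2017 and March 2018.

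On secular change, the Statistical analysis plan section says: "We will include the control condition in the model for severe clinical and clinical pneumonia as a covariate". It names no such adjustment for the other endpoints. Study strengths nevertheless expects the serotype-specific urine assay to establish the indirect effect of PCV13 on VT pneumonia, and presents the phased rollout as a means of comparison between and within districts.

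**The concern.** The primary analysis has unexposed months and a staggered rollout, so a PCV13 term can be separated from a time trend. The prospective-only endpoints have neither, because rollout was complete a year before their data begin. A variable named time since PCV13 introduction looks like a vaccine-exposure measure, but within a district it advances one month per calendar month.

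Any change over 2019–2022 in admission practice, viral circulation or enrolment would therefore enter the same coefficient as a vaccine effect. The protocol expects such change: it says that COVID-19 effects on admissions from 2020 must be accounted for. A secular decline could be taken for indirect protection, and a secular rise could hide it.

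**Working it through.** **Inputs.** Introduction dates from Study setting, window from Study design, month counts from the Statistical analysis plan section.

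**Reproducing the plan's month counts.** Number months from January 2015 = 0. Introductions fall at 17 (June 2016, two districts), 30 (July 2017) and 38 (March 2018). March 2022 is month 86, so there are 87 months. Post-introduction months are 87 − 17 = 70, 87 − 30 = 57 and 87 − 38 = 49. These match the plan's 17/70, 30/57 and 38/49.

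**Prospective window.** March 2019 is month 50, so the window has 86 − 50 + 1 = 37 months, or 148 district-months.

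| District | Introduction month c | Time since introduction, first to last month |
|---|---|---|
| Songinokhairkhan, Sükhbaatar | 17 | 33 to 69 |
| Bayanzürkh | 30 | 20 to 56 |
| Chingeltei | 38 | 12 to 48 |

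No district has an unexposed month.

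**Fixed district effects, linear time.** For district d and month t:

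α_d + β(t − c_d) = (α_d − βc_d) + βt

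The constant is absorbed by the district effect, so β is the calendar slope. If a calendar term γt is added, only β + γ is identified. Numerically:
- District (4 columns), calendar month and time since introduction have rank 5 of 6. R² of time since introduction on the other terms is 1.000.
- With 36 month indicators in place of linear time, rank is 40 of 41.
- On one simulated data set, Poisson fits with either time variable gave the same slope (−0.1269), standard error (0.0206) and log-likelihood.
- The primary design, with its pre-vaccine months, has full rank (6 of 6).

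**Random district intercept.** Aliasing is no longer exact. Assume 3,500 prospective cases (the Discussion's estimate) spread equally over the district-months, and a secular slope of −0.10 per year on the log rate with no PCV13 effect. The between-district SD is also an assumption.

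| Assumed between-district SD | Slope on time since introduction | SE without calendar term | SE with calendar term |
|---|---|---|---|
| 0.05 | −0.082 | 0.017 | 0.040 |
| 0.1 | −0.093 | 0.018 | 0.071 |
| 0.2 | −0.098 | 0.019 | 0.136 |
| 0.4 | −0.100 | 0.019 | 0.269 |

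Between 82% and nearly 100% of the secular slope appears as the PCV13 time slope. Adding a calendar term leaves the separation to level differences among four districts with three distinct introduction dates, and the standard error grows about 2-fold to 14-fold (0.040/0.017 to 0.269/0.019).

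**Non-linear time.** Curvature is estimable in principle: a quadratic adds one rank (41 of 42 with month indicators). But R² of the log or squared term on district and month is 0.96 to 0.97, so little information remains.

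**Early versus late.** The two periods are the same calendar years in every district, so the contrast is also purely calendar.

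**The case against.** - **The article does not specify fixed effects or linear time.** This is right. A reader might infer that aliasing is exact as written, but the sentence does not say so, and the only district term that the article specifies is the random effect in the primary model. Exact aliasing is conditional. What remains under a random effect is near-complete dependence on calendar time.
- **The text promises only to explore trends, and a separate analysis plan holds the detail.** The sentence names no test or effect measure, so it does not itself call the coefficient a vaccine effect. The objectives and Study strengths do make the PCV13 claim. An unseen plan can settle the specification and add comparators, but it cannot supply unexposed months.
- **Other evidence is planned.** A reader might infer that secular change is ignored for these endpoints. It is not. The plan compares PCV13 with non-PCV13 serotypes between years one and three, and runs a VT versus non-vaccine-type (NVT) case-control analysis on household vaccination. It also records policy changes and restrictions, and enrols only SARS-CoV-2-negative cases. These are partly controlled evidence, but they do not change what the trend coefficient means.
- **Simulated rejection rates are no measure of error here.** A reader might want a false-positive rate. Any such figure only shows that a trend test detects an assumed trend at assumed counts, and Poisson counts do not represent carriage detection or density. None is relied on here.

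**Conclusion.** The point holds for the radiological, definite pneumococcal, VT, carriage and RSV/influenza endpoints. Their trend coefficient describes calendar change after introduction and does not estimate an association with PCV13 or an indirect effect. The fixed-effects result is algebraic and needs no assumed counts. The random-effect figures rest on the assumed case total, equal spread, secular slope and between-district SDs. The size of any resulting bias is unknown, because it equals whatever secular trend occurs.

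The point does not reach the primary endpoint, clinical pneumonia or hypoxic pneumonia, all of which have data from 2015. Nor does it show that the planned trend analyses are without descriptive value.

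**What to change.** 1. In Study objectives, the Statistical analysis plan section and Study strengths, state that for these endpoints the coefficient is a descriptive post-introduction calendar trend and not an estimate of PCV13 association or indirect effect.
2. For VT pneumonia, base any PCV13-specific inference on a within-hospital comparator over time: VT against NVT pneumonia, against antigen-negative pneumonia, or both, in a binomial model with district and time. This extends the planned serotype comparison. State the assumption that the comparator shares the secular forces acting on VT pneumonia and, for NVT, that serotype replacement may move it.
3. As a sensitivity analysis, extend the control-condition covariate to the secondary incidence endpoints. Cardiovascular and renal admissions are already being collected at all four hospitals through 2022. State that this addresses secular change only in part and does not remove the aliasing.

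The cost is wording and a few extra models on data already being collected. The price is a weaker claim for these endpoints. The comparator in item 2 serves VT pneumonia only, so the radiological, carriage and viral trends stay descriptive.
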